## Abstract

**Background:**

In low-income countries, only about a third of Human Immunodeficiency Virus/Acquired Immune Deficiency Syndrome (HIV/AIDS) patients eligible for anti-retroviral treatment currently receive it. Providing decentralized treatment close to where patients live is crucial to a faster scale up, however, a key obstacle is limited health system capacity due to a shortage of trained health-care workers and challenges of integrating HIV/AIDS care with other primary care services (e.g. tuberculosis, malaria, respiratory conditions). This study will test an adapted primary care health care worker training and guideline intervention, Practical Approach to Lung Health and HIV/AIDS Malawi (PALM PLUS), on staff retention and satisfaction, and quality of patient care.

**Methods/Design:**

A cluster-randomized trial design is being used to compare usual care with a standardized clinical guideline and training intervention, PALM PLUS. The intervention targets middle-cadre health care workers (nurses, clinical officers, medical assistants) in 30 rural primary care health centres in a single district in Malawi. PALM PLUS is an integrated, symptom-based and user-friendly guideline consistent with Malawian national treatment protocols. Training is standardized and based on an educational outreach approach. Trainers will be front-line peer healthcare workers trained to provide outreach training and support to their fellow front-line healthcare workers during focused (1-2 hours), intermittent, interactive sessions on-site in health centers. Primary outcomes are health care worker retention and satisfaction. Secondary outcomes are clinical outcomes measured at the health centre level for HIV/AIDS, tuberculosis, prevention-of-mother-to-child-transmission of HIV and other primary care conditions. Effect sizes and 95% confidence intervals for outcomes will be presented. Assessment of outcomes will occur at 1 year post- implementation.

**Discussion:**

The PALM PLUS trial aims to address a key problem: strengthening middle-cadre health care workers to support the broader scale up of HIV/AIDS services and their integration into primary care. The trial will test whether the PALM PLUS intervention improves staff satisfaction and retention, as well as the quality of patient care, when compared to usual practice.

**Trial Registration:**

Current controlled Trials: ISRCTN47805230

## Introduction

In 2008, UNAIDS estimated that 33 million people were living with HIV/AIDS [1]. Recent years have seen substantial improvements in access to antiretroviral treatment (ART). For example, in Malawi, a low-income African country, about 170,000 adults and children were alive and on ART in June 2009 [2]. The number of new ART initiations has increased year over year, yet worldwide, only about one-third of HIV patients who need ART are currently getting it [1]. Substantial efforts are now underway to further scale-up HIV/AIDS treatment in Malawi [2] and other resource-poor countries [1], and one key strategy is improving the scale and equity of access by decentralizing HIV/AIDS services to rural primary care centers [1,2].

A key obstacle to scaling up is health system capacity due to a shortage of trained workers in countries like Malawi. It has been estimated that Sub-Saharan Africa would require two times its current human resources to be added every year for the next 10 years to reach universal coverage for HIV/AIDS [3]. The goal of ensuring equitable access to quality health care is further hindered by the difficulty of retaining staff in rural areas of low- and middle-income countries; Malawi in particular has a HCW vacancy rate of 50% [4]. There is wide agreement that closing these gaps will require innovative strategies to optimize the use of existing human resources, and interventions to train and retain staff [4].

Attention to the quality of clinical care provided for HIV/AIDS and other primary care conditions while increasing access to HIV/AIDS services is also important. This is especially so since the workload inherent in a scale-up of access to HIV/AIDS services may have unintended negative consequences on existing primary care services in those same centers [3,5]. This study will test an adapted clinical guideline and training approach, Practical Approach to Lung Health and HIV/AIDS in Malawi (PALM PLUS), to strengthening the health care workforce in a primary care setting where HIV/AIDS services are being decentralized. PALM PLUS is designed to support mid-level HCWs, i.e. nurses and non-physician clinicians (in Malawi, medical assistants and clinical officers), with the overall goal of improving equitable access to quality HIV/AIDS care and primary care services. The primary objectives of the intervention are to improve mid-level HCW retention in rural health centres and improve their job satisfaction; secondary objectives are to improve patient outcomes. Our hypotheses are that the PALM PLUS intervention will be associated with: 1) improved staffing and staff satisfaction, and 2) improved patient outcomes.

## Methods/Design

### Study Design

A population-based unblinded stratified cluster randomized controlled trial design will be used to evaluate the PALM PLUS intervention. Health centers were selected as the unit of randomization in order to minimize contamination of program delivery as well as for logistical and pragmatic reasons. Outcomes of interest are at both the cluster and individual HCW's levels.

### Study Setting

The study is set in Zomba district, Malawi. *Inclusion criteria: *Clusters: All government, mission and institutionally funded health centers offering primary care services to the general public in the district (n = 30) are eligible (health centers are defined as those delivering primarily out-patient primary care, without elective surgeries or in-patient admissions of the general public, and ); individuals: all health professional staff eligible to provide clinical services within the randomized health centres will be included. *Exclusion criteria: *Cluster: none; individual HCWs: refusal to participate.

### Method of randomization

Health centres will be randomized to the intervention (PALM PLUS) or the control arm (see Figure 1). Random allocations will be generated by the random selection option in the Minitab software program. Randomization will be done using two strata with two levels each. Prior to randomization, health centers will be stratified according to funding source (government funded, n = 15; vs. mission or institutionally funded, n = 15); and health centre size as defined by the number of health centre clinical staff postings defined as doctor, nurse, clinical officer or medical assistant working in the clinic at baseline (levels defined as < median number of HCW for all health centers or ≥median number). All health centers are under the supervision of the Ministry of Health's (MoH) District Health Office (DHO), submit performance data to the DHO, and all staff receive standard MoH training and supervision. This stratification is chosen because there may be subtle management, organizational, and motivation differences in government vs. mission/institutionally funded clinics, and larger staff numbers is a proxy for greater complexity of clinical programming and resources, as well as to ensure balance in terms of numbers of HCWs in both study arms. Randomization within strata will be restricted to ensure equal balance in intervention and control sites by health centre type.

**Figure 1 F1:**
[figure not shown]
**Stratified randomization schematic, strata for randomization to intervention and control arm**.

### The Intervention

The intervention centers on the PALM PLUS guidelines and adapted training method, which are a Malawi-specific adaption of the proven PALSA PLUS guidelines implemented in South Africa [6]. PALM PLUS guidelines are symptom-based, integrated guidelines for HIV/AIDS, tuberculosis and common primary care conditions. They have been modified to comply with existing Malawian national disease and condition-specific guidelines, and through consultations with Ministry of Health personnel (at local and national levels), front-line Malawian nurses and clinical officers, and other stakeholders like the Medical Council of Malawi and the Nursing and Midwifery Council of Malawi. The reviewers are expected to check that the content is correct and appropriate and that the algorithms flow properly and reflect available drugs/resources in Malawian Health Centers. Guideline and algorithm development will follow a collaborative and iterative development process to ensure local relevance to front-line healthcare workers, to promote local ownership and to facilitate identification and resolution of any barriers to its implementation (e.g. inadequate access to diagnostic investigations for excluding TB). Key messages covering the content have been developed; these are short, summary information vectors, which provide a content framework for otherwise learner-directed teaching, and which are simple enough to be easily remembered during patient consultations.

Training follows the proven innovative and evidence-based model called educational outreach [7], a form of *point-of-care *training that provides case-based, on-site training to primary care providers in the clinical settings where they work. Trainers will be front-line peer healthcare workers (from government or mission/institutional health centers) who will be trained to provide outreach training and support to their fellow front-line healthcare workers during focused (1-2 hours), intermittent, interactive sessions. Two Master Trainers will be responsible for the initial facility-trainer training, which is conducted offsite during a one-week intensive course in which the facility trainers are equipped with the necessary content, and their training skills developed and evaluated using an iterative process of training and feedback.

Trainers will be expected to lead between 6 to 10 training sessions at each health centre, targeting all nursing and clinical staff working at the health centre, over a maximum period of 12 weeks, but they may conduct additional training sessions if they wish. Point-of-care guideline tools will be developed and distributed (e.g a thin (about 30 pages) sturdy laminated ring binder containing the entire guideline, colourful and easy to follow algorithms designed to be on the primary care provider's desktop during each patient encounter, as well desk blotters with key PALM PLUS messages.

### Control sites

No PALM PLUS materials or training will be provided to personnel working at control health centers. Routine ongoing health centre supervision by District Health Office (DHO) personnel and off-site DHO training courses will continue in all sites.

### Outcome measures

Our primary outcomes will be measured at the cluster (health centre) and individual (staff) levels and relate to clinical staffing (clinical officers, medical assistants, nurses): 1) retention (staff continuing to work in same health centre), 2) total staffing (total of retention/recruitment/loss), and 3) staff satisfaction at the cluster and individual level. Secondary outcomes are clinical outcomes targeted by the PALM PLUS guideline measured at the health centre level: 1) total patient visits, 2) use of cotrimoxazole prophylaxis among HIV+ pregnant women, 3) HIV testing among pregnant women, 4) ART provision among HIV+ pregnant women, 5) Non-ART prevention-of-mother-to-child-transmission treatment provided to HIV+ pregnant women, 6) new adult ART initiations, 7) new adult TB treatment initiations, 8) new adult TB treatment initiations among ART patients, 9) new HIV diagnosis among TB patients, 10) new ART initiations among TB patients, 11) administration of malaria treatments. We will also evaluate competing pediatric primary health priorities as potential unintended consequences (since PALM PLUS targets only the care of adults): 1) total and measles-specific immunizations given 0-5yrs, 2) new ARV initiations among children, 3) HIV tests among children.

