#### Analysis plan

In cluster randomized controlled trials with relatively few clusters, it is recommended to assess the effectiveness of randomization as a first step. Therefore, we will first examine the balance of baseline characteristics of the health centre clusters and the individual patients across intervention groups. Analyses will be done at both cluster (health centre) and individual (health care worker) levels, adjusted for clustering. At the health centre level (cluster level), we will use multivariable linear regression to compare mean staff satisfaction, staff retention and total staffing, adjusting for potential confounders. At the health worker level (individual level), multivariable regression adjusted for clustering by health centre will be used to compare HCW satisfaction scores. For this analysis, we will only include those HCWs who complete a survey at baseline and the appropriate outcome time point and are working in the same health center. Cox regression modeling will be used to estimate the survival probabilities of health care workers (proportion of days employed at health centre over two years of follow-up) to compare 'survival' (sustained days of work at same health centre) across intervention groups, adjusting for potential confounders. Health centre level analyses will use multivariable linear regression to compare secondary outcomes such treatment initiation (ARV, cotrimoxazole, TB, malaria etc.). Treatment initiation will be calculated as the number of patients placed on "X" treatment over the denominator of "Y" health centre referral population. To adjust for cluster randomization, we will use generalized estimating equation binomial regression models with log link and exchangeable correlation structures to estimate the relative risks (RR) and 95% confidence intervals for 'survival' rates (proportion of days employed at health centre over two years of follow-up) between the intervention group (receive PALM PLUS) with the control group as a reference. SAS version 9.2 (SAS Institute Inc, 2008) will be used for all analyses. All analyses will be conducted using the intention to treat principle.

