#### Sample size Calculations

At a two-sided alpha of 0.05 and holding power at 80%, using an estimated value for the intracluster correlation coefficient (ICC) of 0.15, and p1 of 0.90 and p2 of 0.65, an inflation factor of 0.15 and an average cluster size of 5 workers then 67 workers will be required per study arm (the sample size unadjusted for clustering is 42 workers). Inflating this by 10% to ensure a sufficient number of staff have completed multiple longitudinal satisfaction surveys within the same health center, brings the required sample to 74 workers which is equivalent to needing 15 clusters (health centers) per study arm. Rationale for ICC: The ICC is almost always unknown prior to conducting a study. In this instance we have chosen an estimate for the ICC to be 0.15. The rationale for the selection of this ICC value is that previous studies have shown higher ICC values for process variables (e.g., health worker days) compared to outcome variables in the primary care setting [9] and in a previous study which summarized the median ICC from several studies using process variables, the median was found to be 0.2 [10].

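### The protocol names two primary outcomes in some places and three in another, and plans six unranked analyses of them, while the sample size spends an undivided 0.05 on one comparison whose outcome is not named.

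*Protocol article*

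**What the plan says.** **Which outcomes are primary.** The abstract states: "Primary outcomes are health care worker retention and satisfaction". The Introduction agrees: "The primary objectives of the intervention are to improve mid-level HCW retention in rural health centres and improve their job satisfaction". The Outcome measures section adds a third: "1) retention (staff continuing to work in same health centre), 2) total staffing (total of retention/recruitment/loss), and 3) staff satisfaction". The same section says: "Our primary outcomes will be measured at the cluster (health centre) and individual (staff) levels".

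**How they are analysed.** The Analysis plan states: "Analyses will be done at both cluster (health centre) and individual (health care worker) levels, adjusted for clustering". At cluster level, "we will use multivariable linear regression to compare mean staff satisfaction, staff retention and total staffing, adjusting for potential confounders". It then adds an individual-level regression of satisfaction scores allowing for clustering, a Cox model for time worked at the same centre, and a GEE binomial model with log link for the relative risk of the same kind of retention quantity. No model or level is called primary.

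**When.** The Ascertainment of outcomes section makes 12 months against baseline the main comparison and describes the 2-4 month survey as an immediate evaluation. The abstract also gives one year. The Cox and GEE sentences in the Analysis plan refer to two years of follow-up.

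**What was sized.** The Sample size Calculations section begins "At a two-sided alpha of 0.05 and holding power at 80" (per cent) and compares 0.90 with 0.65, without saying which outcome these proportions describe.

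**The concern.** Total staffing is not another name for retention. Recruitment can raise total staffing while retention falls, so whether it is primary changes what the trial can claim. The text as it stands supports either answer.

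Retention has three analyses and satisfaction has two, with nothing to say which one settles the question. If the cluster-level regression and the Cox model disagree, the document gives no rule for resolving it. A reader of the results could not tie a positive claim to one pre-specified 5% test, because any of several results could be put forward as the primary one. The sample size, by contrast, was worked out for a single test at the full 0.05.

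**Working it through.** **1. The plan's own figure.** Inputs from Sample size Calculations: proportions 0.90 and 0.65, two-sided alpha 0.05, power 80%, ICC 0.15, 5 workers per cluster, 10% inflation.

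- Unadjusted, pooled normal formula: n = [1.960 × √(2 × 0.775 × 0.225) + 0.842 × √(0.09 + 0.2275)]² / 0.25² = 42.6 per arm. The plan states 42.
- Design effect: 1 + (5 − 1) × 0.15 = 1.6.
- 42 × 1.6 = 67.2; 67.2 × 1.10 = 73.9; 73.9 / 5 = 14.8, so 15 clusters per arm.

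This matches the plan's 67, 74 and 15. The sample size is sound for one comparison at 0.05.

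**2. Count of primary-outcome analyses at the main time point.**

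| Outcome | Analyses in the Analysis plan | Number |
|---|---|---|
| Retention | cluster-level linear; Cox; GEE log-binomial | 3 |
| Satisfaction | cluster-level linear; individual-level regression | 2 |
| Total staffing | cluster-level linear | 1 |
| Total | | 6 |

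**3. Chance of at least one false positive, each judged at 0.05.** Under independence it is 1 − 0.95^k:

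- k = 2 (abstract): 1 − 0.95² = 9.75%
- k = 3 (Outcome measures): 1 − 0.95³ = 14.3%
- k = 6 (all analyses): 1 − 0.95⁶ = 26.5%

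The outcomes overlap, and several models use the same workers, so positive correlation is expected. The document gives no correlations; those below are assumptions. Results come from simulating equally correlated two-sided z-tests (1,000,000 draws).

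| Assumed correlation | 3 outcomes | 6 analyses |
|---|---|---|
| 0 | 14.3% | 26.5% |
| 0.5 | 12.5% | 20.8% |
| 0.8 | 9.8% | 13.9% |
| 0.9 | 8.3% | 10.8% |

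Every case exceeds 5%.

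**4. Splitting alpha or setting an order.** Splitting 0.05 three ways (0.0167 each) gives 58 per arm unadjusted; 58 × 1.6 = 92.8; × 1.10 = 102.1; / 5 = 20.4, so 21 clusters per arm, 42 in all. The Study Setting section has 30 eligible centres, all already used. At the planned 74 per arm (effective size 74 / 1.6 = 46.25), power for 0.90 against 0.65 is 83% at 0.05 and 69% at 0.0167. A fixed order keeps 0.05 for the first test and leaves the sample size alone.

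**The case against.** The strongest reply is that this is largely an omission. A condensed protocol article commonly leaves the multiplicity rule and the choice of primary model to an analysis plan, and none is shown. That holds for the absence of an alpha rule taken alone. It does not answer the conflict between two and three primary outcomes, nor the fact that this text chose to specify several models for the same outcome without ranking them. Those are on the page.

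Second, 0.05 appears only in the sample-size section, and the abstract promises effect sizes with 95% confidence intervals rather than tests. This stands as a caveat: judging each outcome at 0.05 is inferred from the undivided alpha and the 95% level. If all primary outcomes had to be positive, there would be no inflation across outcomes, but the document states no such rule.

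Third, the GEE sentence can be read as the way clustering is allowed for rather than as a further claim, which would make six slightly too many. The conclusion would not change.

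A reader might go further and count eight tests, adding satisfaction at 2-4 months at both levels, for a familywise error of 1 − 0.95⁸ = 34%. The documents do not support this. Twelve months is already the main comparison, so the early survey is subordinate, and independence is unrealistic for models fitted to the same workers. Nor is every outcome analysed at two levels: total staffing has only a cluster-level model. A reader might also say that a three-way alpha split cuts power from 79% to 64%. Those values are for 67 per arm, before the plan's 10% inflation; at the planned 74 they are 83% and 69%.

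**Conclusion.** The point holds. The document contradicts itself on the number of primary outcomes and fixes six unranked analyses of them, against a sample size for one unnamed comparison at an undivided 0.05. If each result is judged at 0.05 and any one positive result counts as success, familywise error is about 10% to 14% for three outcomes (assumed correlation 0.8 to 0) and about 11% to 27% for six analyses (0.9 to 0). Both conditions are inferred, and the correlations are assumed. The sample-size arithmetic is not at fault. The two-versus-three conflict and the unranked models need no assumption, and should be corrected.

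**What to change.** 1. Make the abstract, the Introduction and the Outcome measures section agree on the primary outcomes, and say whether total staffing is one.
2. Name one deciding analysis for each primary outcome: level, model and time point. For retention this means choosing among the linear, Cox and GEE analyses, and reconciling the 12-month main comparison in Ascertainment of outcomes with the two-year retention analyses in the Analysis plan.
3. Fix a testing order at two-sided 0.05 before results are seen. One option is retention, then satisfaction at 10-12 months, then total staffing if it is kept as primary, stopping at the first non-significant result. The particular order is the investigators' choice; what matters is that one is written down.
4. Label the remaining models and levels as supporting.
5. State which outcome the 0.90 against 0.65 calculation and its 80% power refer to. The ICC rationale points to retention, while the 10% inflation is for repeated satisfaction surveys, so the text does not settle it.

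Cost: wording only, with no change to the sample size. The downside is that a later outcome cannot be claimed if an earlier one fails.

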### Ascertainment of outcomes

Outcomes will be ascertained at baseline and during monthly visits to all health centers; main comparison will be at 12 months vs. baseline;. The clinical manager will be interviewed each visit to determine ongoing employment, and dates of new arrivals and departures of clinical staff. A validated staff satisfaction survey [8] will be administered to clinical staff (at baseline, 2-4 months [for immediate staff satisfaction/retention evaluation], and 10-12 months [late outcomes], ensuring that data is collected for approximately the same calendar months at study and control sites. Patient outcomes will be determined by monthly review of health centre registers and/or patient treatment cards.

